#### Questionnaires

Older people receiving HCS, their relatives and care staff (intervention and control groups) will be asked to complete a questionnaire covering demographics and study endpoint variables at baseline and at 12- and 24-month follow-up. Study outcomes for older people, relatives and staff will be measured using the following questionnaires, see Table 1.

**Table 1 Tab1:** Overview of participants, outcomes and questionnaires

Participants	Outcome	Questionnaires
Older people	Health and QoL (primary outcomes)	Nottingham Health profile, EQ-5D
	Thriving	The Thriving of Older People Assessment Scale
	Satisfaction with care Involvement in decisions and care Personal activity of daily living	Quality of Care from the Patient’s Perspective Impact on Participation and Autonomy – Older Persons The KATZ ADL index
Relatives	Caregiver burden	Caregiver Burden Scale
	Satisfaction with care	The Pyramid Questionnaire
	Informal caregiving engagement	The Resource Utilization in Dementia
Personnel	Job satisfaction	The Measure of Job Satisfaction
	Stress of conscience PCC	The Stress of Conscience Questionnaire The Person-Centered Care Assessment Tool

#### Primary outcomes

Two primary outcomes will be measured, self reported health and QoL. The first primary outcome will be measured using the Nottingham Health Profile, which is a scale that includes 38 items and consists of 6 dimensions: energy level; pain; emotional reaction; sleep; social isolation; and physical abilities. Each item is presented as a statement with a Yes/No response and the score ranges from best (0) to worst (100) possible [45]. The Nottingham Health Profile has been found to be sensitive to change, and both valid [45] and reliable [49].

The second primary outcome will be measured using the EQ-5D scale, which comprises two parts, a state of health description, which includes 5 items and a visual analogue scale. The state of health description comprises five dimensions: mobility; self-care; usual activities; pain/discomfort; and anxiety/depression. Each dimension is scored on a five-level Likert-scale ranging from none (0) to extreme (4). The visual analogue scale rates participants’ overall health between endpoints, from worst imaginable health (0) to best imaginable health (100). EQ-5D has been found to be both sensitive to change and valid [50].

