### Power calculations

Sample size calculations for the primary endpoint (NHP) [45], for older people indicate that a sample of *N* = 207 will provide 85% power at the 0.05 significance level to detect case control mean differences of 6, based on previously reported results on the dimension social isolation [46]. Further power calculations indicate that the study is sufficiently powered to detect significant differences for the other National Health Profile (NHP) dimensions and also for the secondary endpoints. To adjust for a drop-out rate of 29% based on study by Rokstad et al. [40], 270 participants will be recruited.

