### Data analyses

#### Statistical analyses

The SPSS 22.0 for windows (SPSS Inc., Chicago, IL) will be used for all statistical analyses Data concerning the participants’ personal characteristics will be analysed using descriptive statistics. Differences between groups will be analysed using Independent sample *t*-test or the Mann-Whitney *U*-test for continuous data and the Chi-square test for dichotomised data. Changes within the two groups will be analysed separately using the paired *t*-test or Wilcoxon Signed Rank Test for continuous data and the McNemar test for dichotomised data. In addition, statistical regression models adjusting for background characteristics and account for correlated measurements for the same individual will also be used (e.g., mixed effects model and generalized estimating equations). A *p*-value of *<*0.05 will be regarded as statistically significant and effect sizes will be estimated with Cohen’s d [63]. All data analysis will be performed on an intention-to-treat principle.

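### Two multi-part primary outcomes share an unadjusted 0.05 threshold with no success rule, while the sample size covers one NHP endpoint and gives EQ-5D no stated power

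*Protocol article*

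**What the plan says.** The protocol article is explicit about the number of primaries. Under Primary outcomes it says "Two primary outcomes will be measured, self reported health and QoL". The abstract and Table 1 agree.

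- The first primary is the NHP, which "consists of 6 dimensions: energy level; pain; emotional reaction; sleep; social isolation; and physical abilities". No total score or lead dimension is named in that section.
- The second is EQ-5D, "which comprises two parts, a state of health description, which includes 5 items and a visual analogue scale". Neither part is named as the endpoint.
- Questionnaires are completed "at baseline and at 12- and 24-month follow-up". Neither follow-up is named as primary.
- Under Statistical analyses there is one threshold for everything: a p-value below "0.05 will be regarded as statistically significant". No alpha split, testing order or success rule accompanies it.

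Power calculations uses the singular, "Sample size calculations for the primary endpoint (NHP"), and states that a sample of 207 "will provide 85% power at the 0.05 significance level to detect case control mean differences of 6", based on earlier results for social isolation. It adds, without figures, that power is also sufficient for the other NHP dimensions and for the secondary endpoints.

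**The concern.** Two things do not fit together.

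First, the power section has one primary endpoint and the outcomes section has two. The supplementary power claims cover the remaining NHP dimensions and the secondary endpoints. EQ-5D is a declared primary, so it belongs to neither group and has no stated power. If it was meant to fall among the secondary endpoints, the power section contradicts the outcomes section.

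Second, two primaries judged at 0.05 each, with no statement that both must succeed, give more than a 5% chance of at least one false-positive primary result. The chance rises further if dimensions, EQ-5D parts and visits are tested separately. The claim of adequate power for the other NHP dimensions suggests that dimension-level tests are foreseen.

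At stake is what counts as a positive trial. Left open, the supporting score and visit could be chosen after the data are seen. In a non-randomised comparison of two districts, prespecification is one of the few protections available.

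**Working it through.** **Inputs from the protocol article.** Two primaries; six NHP dimensions; two EQ-5D parts; two follow-ups; threshold 0.05; mean difference 6; power 85%; N = 207; 270 recruited; drop-out 29%.

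**Assumptions.** Two-sided tests. N = 207 is per arm, the natural reading because 270 is the number per group. Each single test truly holds its 5% level. Correlation is 0.3-0.7 between scores and 0.5-0.7 between visits; the article gives none.

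**Step 1: the plan's own figure.** No SD is given, so 207 cannot be reproduced, only solved backwards from n = 2·SD²·(1.960 + 1.036)²/6² per arm:

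- SD = 6 × √(207/2) / 2.996 = 20.4 if 207 is per arm.
- SD = 6 × √(103.5/2) / 2.996 = 14.4 if 207 is the total.

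The calculation uses the whole 0.05 for one endpoint.

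**Step 2: chance of at least one false-positive primary result.** For k independent tests this is 1 − 0.95^k. The correlated figures come from simulating multivariate normal test statistics (400,000 draws).

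| Reading | k | Independent | Correlated |
|---|---|---|---|
| One score per outcome, one visit | 2 | 9.75% | 8.3-9.5% |
| One score per outcome, both visits | 4 | 18.5% | 13.8-17.0% |
| Six NHP dimensions, EQ-5D description, VAS, one visit | 8 | 33.7% | 19-30% |
| The same eight scores, both visits | 16 | 56.0% | 30-48% |

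The within-group tests and regression models that the article also lists are not counted.

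**Step 3: power if the two primaries share alpha.** At the first Holm step alpha is 0.05/2 = 0.025, with critical value 2.241. Power ≈ Φ(6 / (20.37 × √(2/n)) − 2.241).

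- n = 207: Φ(3.00 − 2.24) ≈ 77-78%, against 85% at 0.05.
- n = 192 (270 × 0.71 = 191.7, the number left after the stated 29% drop-out): Φ(2.89 − 2.24) ≈ 74%.
- Restoring 85% at alpha 0.025 needs 2 × 20.37² × (2.241 + 1.036)² / 36 ≈ 248 analysed per arm.

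If 207 were the total (SD 14.4) and 192 per arm were analysed, the same formula gives Φ(4.08 − 2.24) ≈ 97%. The power cost therefore depends on the unstated SD. These are first-step figures for social isolation; if EQ-5D is rejected first, Holm then tests NHP at the full 0.05.

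**The case against.** The strongest reply is that this is an article. The exact score, the visit and the testing hierarchy are commonly left to the full protocol or analysis plan, so their absence alone is no fault. That is fair, and the point does not rest on it. It rests on what the article does fix: two primaries in one section and one in another, a general 0.05 threshold, and power claims that pass over one declared primary. An analysis plan cannot reconcile the sections without departing from one of them.

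A both-must-succeed rule would remove the inflation between the two outcomes. That is correct, but no such rule is stated.

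Several stronger inferences are tempting and are not supported:

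- **That there are at least 16 primary tests.** The article states no number. Sixteen is the product of one wide reading. The article also mentions mixed models and generalized estimating equations, so the two visits might be handled in one model.
- **That a false-positive primary result is more likely than not.** Only the 16-test independent case exceeds 50%. Independence is implausible for overlapping health scores from the same people, and the correlated range for that reading is 30-48%.
- **That power is claimed for one test only.** The article also claims it for the other NHP dimensions and the secondary endpoints, though without figures. EQ-5D is the gap.
- **That 24 months asks a different question because the service has taken over by then.** The first phase lasts 10 months, so the 12-month visit also falls after the handover, and the research team continues to give support.

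**Conclusion.** The point holds. On any reading in which either primary may succeed, the error rate for a primary claim exceeds the nominal 5%. It is about 8-10% on the narrowest reading, about 14-19% with one score per outcome at both visits, and about 30-56% if all eight scores are tested at both visits. The article does not say which reading applies, so the size is a range. Its lower ends rest on assumed correlations and its upper ends on independence.

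Separately, and without any assumption, the power section and the outcomes section disagree on the number of primary endpoints, and EQ-5D has no stated power. The loss of power from sharing alpha (85% to about 77-78%, or about 74% after the stated drop-out) depends on 207 being per arm and on the back-solved SD of about 20.4.

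**What to change.** Reconcile the power and outcomes sections before outcome data are examined:

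1. Name one score for each primary outcome. For NHP, social isolation is the dimension on which the study is sized. For EQ-5D, choose one part.
2. Name one primary visit.
3. Test the two primaries with Holm, or state that both must succeed, each at 0.05.
4. Make the remaining NHP dimensions, the other EQ-5D part and the other visit secondary.
5. Restate the power with the SD and a per-arm label, and give EQ-5D its own power statement.

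The alternative is a single primary score at one visit. This keeps alpha at 0.05 and N at 207, but demotes the other outcome. If EQ-5D is the one demoted, note that QoL comes first in the study's overall aim, so the choice belongs to the investigators.

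The cost is wording only; no new data are needed. Fewer results can be called confirmatory, and stated power falls. Under Holm the first-step figures are those in the working. Under a both-must-succeed rule there is no alpha loss, but joint power cannot exceed that of the weaker outcome. For example, if both had 85% and were independent, it would be 0.85 × 0.85 ≈ 72%.

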#### Secondary outcomes

Ten secondary outcomes will be explored, thriving, quality of care, impact on participation and autonomy, ADL-function, caregiver burden, satisfaction, resource utilisation, job satisfaction, stress of conscience and person-centredness of care. The first secondary outcome will be measured using the Thriving of Older People Assessment Scale which includes 32 items and consists of five sub-scales: resident attitude towards the place they were currently living in; quality of the care and care-givers; activities and peer relationships; opportunities to keep in touch with people and places of importance; and qualities in the physical environment. Each item has six possible responses on a Likert-scale, ranging from No (1) to Yes, I agree completely (6). The Thriving of Older People Assessment Scale has been found to be valid and reliable [51].

The second secondary outcome will be measured using the Quality of Care from the Patient’s Perspective, a scale which includes 64 items and comprises four dimensions: medical-technical competence (11 items); physical-technical conditions (10 items); identity-oriented approach (30 items); and social-cultural atmosphere (13 items). Each item is to be answered by the respondents in two ways - perceived reality and subjective importance. Perceived reality ranges from Not applicable (1) to Fully agree (5) on a five-level Likert scale while the subjective importance ranges from Of very great importance (1) to Of little importance (4). The Quality of Care from the Patient’s Perspective has been found to be valid and reliable [52].

The third secondary outcome will be measured using the Impact on Participation and Autonomy – Older Person’s questionnaire which includes 22 items and consists of eight dimensions: mobility (5 items); self-care (5 items); activities in and around the house (4 items); financial situation (1 item); financial situation (1 item); social relationship (5 items); help and support others (1 item) and summary (1 item). Each item is scored on a five-point Likert scale: very good (1) to very poor (5). The Impact on Participation and Autonomy –Older Persons has been found to be valid and reliable [53].

The fourth secondary outcome will be measured using the KATZ ADL index [54] which includes 15 items and consists of two dimensions - instrumental ADL and personal ADL. Each item is scored dichotomously dependent (0) or independent (1). The Katz ADL index has been used since 1961, and has proved consistent in evaluating functional status among older people. No formal validation studies have been found in the literature but the KATZ ADL index has been found to be reliable [55].

The fifth secondary outcome will be measured using the Caregiver Burden Scale that includes 22 items and consists of five dimensions: general strain; isolation; disappointment; emotional involvement; and environments. Response alternatives are scored on a four-point Likert-scale, ranging from Not at all (1) to Often (4). The Caregiver Burden Scale has been found to be valid and reliable [56].

The sixth secondary outcome will be measured using the Pyramid questionnaire, which includes 40 items and consists of seven parts: information; staff professional skills; care; activity; contact; social support; and relative participation. Response alternatives are scored on a four-point Likert-scale ranging from Yes, to a great degree to No, not at all. The scale has been found to be both valid and reliable [57].

The Resource Utilization in Dementia instrument will be used to measure the seventh secondary outcome and this scale includes three parts: personal activities of daily living (dressing/undressing, showering/bathing, washing, and moving); instrumental activities of daily living (cooking, shopping, washing, cleaning, taking care of finances, giving medication and transportation); and watching over (risks such as fire, fall indoors etc.). The Resource Utilization in Dementia assesses resource utilization in terms of hours of homecare, number of days in hospital, number of visits to GPs, physiotherapists, and informal care. The instrument has been found to be valid and reliable [58].

The Measure of Job Satisfaction will be used to measure the eighth secondary outcome and this scale includes 37 items and consists of five dimensions: personal satisfaction; satisfaction with workload; team spirit; training; and professional support. Responses are scored on a five-point Likert-scale, ranging from Very dissatisfied (1) to Very satisfied (5). The scale has been found to be valid and reliable [59].

The ninth secondary outcome will be measured using the Stress of Conscience scale, which consists of ten items related to various healthcare situations, each question comprises an A and a B part. The response alternatives in part A are scored on a six-point Likert-scale, ranging from Never (0) to Every day (5). The questions are related to how often different situations arise in the workplace. Part B comprises a ten-centimetre visual analogue scale where the impact of each situation on the participant’s conscience is estimated. A total index can be calculated where a higher value signifies higher levels of stress of conscience. The Stress of Conscience scale has been found to be valid [60].

Finally, the tenth and last secondary outcome will be measured using the Person-Centred Care Assessment Tool (P-CAT), a tool that consists of 13 items concerning the content of care, the environment and organization. The P-CAT will be used to evaluate changes in PCC. Response alternatives are scored on a five-point Likert-scale, ranging from Disagree completely (1) to Agree completely (5). Higher scores indicate a greater degree of PCC. The P-CAT has been found to be both valid and reliable [61].

#### Qualitative research interviews

Qualitative research interviews [62] will be utilised to explore the participants’ lived experiences of the intervention. The interviews will start with a probing statement such as: Can you please tell me about your experiences of this intervention? What has it meant to you personally? The interviews will be tape-recorded and transcribed verbatim [62, 63].

### Data analyses

#### Statistical analyses

The SPSS 22.0 for windows (SPSS Inc., Chicago, IL) will be used for all statistical analyses Data concerning the participants’ personal characteristics will be analysed using descriptive statistics. Differences between groups will be analysed using Independent sample *t*-test or the Mann-Whitney *U*-test for continuous data and the Chi-square test for dichotomised data. Changes within the two groups will be analysed separately using the paired *t*-test or Wilcoxon Signed Rank Test for continuous data and the McNemar test for dichotomised data. In addition, statistical regression models adjusting for background characteristics and account for correlated measurements for the same individual will also be used (e.g., mixed effects model and generalized estimating equations). A *p*-value of *<*0.05 will be regarded as statistically significant and effect sizes will be estimated with Cohen’s d [63]. All data analysis will be performed on an intention-to-treat principle.

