## Methods/design

A non-randomized controlled trial with a before/after design will be used to explore the effects of the intervention, and a phenomenological-hermeneutic approach to illuminate meanings of the intervention.

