### Participants and setting

All participants will be recruited from one municipality in northern Sweden. Two hundred and seventy older people from one geographical HCS district will be invited to form the intervention group and 270 older people from a different geographical HCS district will be invited to form the control group. Both districts have similar organisations, working conditions, staff skill mix and educational levels. In addition, one relative for each person receiving HCS (*n* = 540) will be asked to participate. Sixty-five HCS staff will be invited to participate in the intervention group and 65 in the control group. The inclusion criteria for the older person will be: 1) aged 65 years or older; 2) living at home and receiving HCS, with at least two visits per month and 3) able to speak Swedish. Inclusion criteria for relatives will be; 1) defined by the older person as his/her relative; 2) able to speak Swedish. Inclusion criteria for staff will be; 1) employed in the HCS district for more than 6 months at baseline, as contact staff and 2) able to speak Swedish. A convenient sub-sample of older people (*n* = 30), relatives (*n* = 30), and HCS staff (*n* = 30) from the intervention group will be invited to participate in qualitative research interviews.

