The principal limitation of this study may well be the lack of randomisation. The intervention introduces an educational programme but also a slightly new process in that person-centred health and care conversations are to be held with care recipients, and that these conversations then are to be used as facilitating change in the way care is provided in those instances that this has been regarded as needed by the participating older people and relatives. To randomize on an individual level introduces several difficulties. Firstly, it is difficult for the same care staff to adopt different procedures and switch between different care models following the randomization of individual care recipients to different groups. To switch between different care models when providing care to different people provide a risk of confusion of what care model to use and jeopardize the adherence to the scheme for intervention and control group. However, cluster randomisation would have been an option, but the municipalities that was available for participation in the study proved to be too small and therefore not able to provide the units needed to make cluster randomisation possible. It will be possible to follow up this study with a larger sample to enable cluster randomisation and higher external validity.

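### The plan tests unadjusted group differences and separate within-arm changes in a non-randomised two-district study, and does not make a between-arm difference in change the deciding result

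*Protocol article*

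**What the plan says.** The design is given under Methods/design: "A non-randomized controlled trial with a before/after design will be used to explore the effects of the intervention". Allocation follows geography. Under Participants and setting, one district supplies the intervention group and "270 older people from a different geographical HCS district will be invited to form the control group". The questionnaires cover "study endpoint variables at baseline and at 12- and 24-month follow-up".

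The Statistical analyses section lists three sets of analyses:

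1. "Differences between groups will be analysed using Independent sample" t-test or Mann-Whitney test, with chi-square for dichotomised data.
2. "Changes within the two groups will be analysed separately using the paired" t-test or Wilcoxon test, with McNemar for dichotomised data.
3. "In addition, statistical regression models adjusting for background characteristics and account for correlated measurements for the same individual will also be used", with mixed models and GEE given as examples.

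One threshold, p<0.05, covers them all. The section does not rank them, and it names no group-by-time term, no difference in change and no adjustment for the baseline value of the outcome. The Discussion says: "The principal limitation of this study may well be the lack of randomisation".

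**The concern.** The first research question asks whether the intervention has significant effects. In a controlled before/after design, the quantity that answers it is the difference between arms in change from baseline. The two simple sets of tests answer other questions, and each has its own weakness.

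- **Unadjusted comparison of follow-up scores.** It removes a time trend common to both districts. It does not remove a difference that existed before the intervention.
- **Paired test within one arm.** It removes that arm's stable baseline level. It does not remove a common trend and makes no comparison with the other arm. Significance in one arm only is not evidence that the arms differ.

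The third set could supply the right contrast, but that contrast is not stated and the models come as an addition. Followed as written, the section allows an effect claim from any of the three, and they can disagree.

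**Working it through.** **The plan's own figure.** Power calculations gives N = 207 for 85% power at the 0.05 level and a mean difference of 6 on the Nottingham Health Profile (NHP) social isolation dimension. No SD is stated, so 207 cannot be reproduced, only solved backwards. Assuming 207 per arm and a two-sided test:

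SD = 6 / [(1.960 + 1.036) × √(2/207)] = 6 / 0.2945 = 20.4

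If 207 were the total for both arms, the SD would be 14.4. The error rates below are worked in SD units, so they depend on the number per arm and not on this choice.

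**Number per arm.** Participants and setting gives 270 older people per group. With the stated 29% dropout, 270 × 0.71 = 191.7, about 192.

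**Unadjusted follow-up test, no true effect.** Assumed: a district gap of 0.2 SD at baseline, of which a fraction f is still present at follow-up.

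- Standard error in SD units: √(2/192) = 0.102
- Type I error = Φ(0.2f/0.102 − 1.96) + Φ(−0.2f/0.102 − 1.96)

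| Fraction persisting | Shift (SD) | Shift in NHP points (SD 20.4) | Type I error |
|---|---|---|---|
| 0.5 | 0.10 | 2.0 | 17% |
| 0.7 | 0.14 | 2.9 | 28% |
| 1.0 | 0.20 | 4.1 | 50% |

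A shift of 2.0 to 4.1 points is 34% to 68% of the 6-point target. A gap of 0.1 SD that persists in full gives the same shift, and so the same 17%, as the first row.

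**Separate paired tests, equal change in both arms.** Assumed: a common standardised change d, in units of the SD of change. The chance of significance in one arm is p = Φ(d√192 − 1.96) + Φ(−d√192 − 1.96). The chance that exactly one of two independent arms is significant is 2p(1 − p).

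| d | d√192 | p | Exactly one arm significant |
|---|---|---|---|
| 0.10 | 1.39 | 0.28 | 41% |
| 0.15 | 2.08 | 0.55 | 50% |
| 0.20 | 2.77 | 0.79 | 33% |

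**Is ANCOVA an equivalent remedy?** Take a fully stable 0.2 SD gap and an assumed baseline–follow-up correlation of 0.5. Adjusting for the baseline score removes only half the gap: 0.2 × (1 − 0.5) = 0.10 SD, or 2.0 points, remains. The standard error is √(2 × 0.75/192) = 0.088 SD, and the type I error is about 20%. The difference in change keeps 5% under a stable gap. The two are not interchangeable here.

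**Precision of the difference in change.** Its variance relative to a follow-up comparison is 2(1 − r). That is 1.0 at r = 0.5 and 0.6 at r = 0.7, so nothing is lost at a correlation of 0.5 or above. At 207 per arm, power for the 6-point difference is 85% and 97% respectively.

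**The case against.** A reader might infer that the effect will be judged by the unadjusted and paired tests alone. The document does not support that. The sentence that follows them plans covariate-adjusted models for repeated measures, the class of analysis this design needs. Nothing is labelled as leading, and nowhere does the plan say that conclusions will rest on significance in one arm only. Nor do both simple tests share both weaknesses; each has one.

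Further points stand in part:

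- **Object of the two-sample tests.** The text does not say whether they apply to baseline, follow-up or change scores. On change scores, a two-sample test is itself the difference-in-change test. The error rates above apply only to follow-up scores.
- **Detail left to a fuller document.** Model terms and covariates may sit in a full protocol or SAP that is not shown, and their absence from an article is no fault. What remains is what the article does state: separate within-arm testing and unadjusted comparison at p<0.05, with the adjusted model as an addition.
- **Comparable districts.** The Abstract speaks of a matched control group, and Participants and setting describes similar organisations and staff. This makes a large gap less likely, but the similarity described concerns the services, not the recipients' baseline health.
- **Limits of the remedy.** The difference in change assumes that the district gap would stay constant without the intervention. If only half of a 0.2 SD gap persisted, it would be off by 0.10 SD in the opposite direction. That supports fixing the choice in advance and checking it in a sensitivity analysis.

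**Conclusion.** The concern holds in a limited form. The plan contains a suitable class of model. It also specifies tests that carry district differences into the effect or do not compare the arms, and it neither says which analysis decides nor states the between-arm difference in change.

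The size is illustrative: 17–50% type I error for an unadjusted follow-up comparison, and 33–50% of studies with exactly one significant paired test. Both ranges assume 192 per arm and two-sided 5% tests. The first also assumes a 0.2 SD gap of which 50–100% persists; the second assumes an equal change of 0.10–0.20 SD of change in both arms. The documents give no SD, gap, correlation or trend, so these figures show what could happen and are not forecasts for this study.

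**What to change.** In the Statistical analyses section:

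1. Name the already planned adjusted longitudinal model as the deciding analysis. Its effect estimate is the group-by-time contrast: the between-arm difference in change from baseline, with a 95% CI.
2. Choose one model family for that role.
3. Label the within-arm paired tests and the unadjusted two-sample tests descriptive, and say that no conclusion about effect rests on them.
4. Do not offer ANCOVA as an equal alternative. Use it at most as a sensitivity analysis, with the differing assumption about the district gap stated.
5. State that, with one district per arm, no model can separate the intervention from other differences between the districts.

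The cost is wording only. Outcomes are already collected at baseline, 12 and 24 months, and no added data or participants are needed.

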#### Operationalization

Thirdly, staff will conduct a person-centred health and care conversation (60 min) with each older person participating in the study. The purpose of these conversations is to evaluate the extent to which current HCS practices meet the older person’s needs, to maintain or rearrange the care plan to provide care that maximises older people’s health and satisfies psychosocial as well as physical needs. The conversation will be documented and used to influence changes in the care plans as well as in daily care. In addition, staff will be encouraged to balance the care plans with the daily needs and priorities of the older person, so that the daily work of staff will be increasingly characterised by flexibility in adapting planned activities to the older person’s current needs. The person centeredness will thus influence both the planning and daily provision of care. For example, showering could be replaced by a visit to the library if the older person regards the latter as being significantly more conducive to his/her QoL at the moment.

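### Staff deliver the intervention and each arm is one district, yet the 85% power and the planned tests allow for no clustering, so both are somewhat too favourable

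*Protocol article*

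**What the plan says.** Participants and setting fixes one district per arm: "Two hundred and seventy older people from one geographical HCS district will be invited to form the intervention group", with the controls drawn from another district. It also plans 65 staff per arm, who must be contact staff. Under Intervention, the training and group supervision go to staff, and "staff will conduct a person-centred health and care conversation (60 min) with each older person participating in the study".

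Power calculations sets the sample at 207 and says that this number "will provide 85% power at the 0.05 significance level to detect case control mean differences of 6". For the basis it cites an earlier study's findings on social isolation, one part of the Nottingham Health Profile. It gives no SD, ICC or design effect, and does not say whether 207 is per arm or in total.

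Statistical analyses compares groups with the independent-sample t-test, Mann-Whitney test or chi-square test. It adds regression models (mixed models and GEE are given as examples) "adjusting for background characteristics and account for correlated measurements for the same individual". The Discussion names the absence of randomisation as the main limitation and explains that too few units were available to randomise clusters.

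**The concern.** The intervention works through staff. Clients of one staff member share that person's skill and their uptake of the training, so their outcomes may be alike. Tests that treat the clients as independent then give standard errors that are too small. The models described would correct for repeated measurements on a person but not for a shared staff member.

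A second problem lies one level up. With one district per arm, anything that changes over 12 to 24 months in one district and not in the other, such as management, staffing or local services, falls entirely on one side of the comparison. No standard error in the plan reflects it. At stake is whether p<0.05 on a primary outcome can be read as an intervention effect at the stated error rate.

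**Working it through.** **Inputs from the article.** Difference 6; power 85%; alpha 0.05; N = 207; 65 staff per arm; 270 older people recruited per arm.

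**Assumptions.** The test is two-sided. The 207 is per arm, which fits its being raised to the 270 recruited per district. Each older person is linked to one contact staff member. The staff ICC is 0.01 to 0.10, and it refers to the quantity actually compared between groups.

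**Step 1: reproduce the plan's figure.** The SD is not given, so it is solved backwards:

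SD = 6 × √(207/2) / (1.960 + 1.036) = 20.4, a standardised difference of 6/20.4 = 0.295.

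With this SD, an individual-level two-sample calculation returns 207 per arm at 85% with no design effect. This shows consistency only. It does not independently confirm the 207.

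**Step 2: cluster size.** Evaluable clients per staff member: m = 207/65 = 3.18.

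**Step 3: design effect, power and type I error.**

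- DE = 1 + (m − 1) × ICC
- Power = Φ(6 / (SD × √(2 × DE/207)) − 1.96)
- True error of the unadjusted test = 2 × (1 − Φ(1.96/√DE))

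| Staff ICC (assumed) | DE | Effective n per arm | Power | True type I error | Evaluable n per arm for 85% |
|---|---|---|---|---|---|
| 0 | 1.00 | 207 | 85.0% | 5.0% | 207 |
| 0.01 | 1.02 | 202.6 | 84.2% | 5.3% | 212 |
| 0.02 | 1.04 | 198.3 | 83.5% | 5.5% | 217 |
| 0.05 | 1.11 | 186.6 | 81.2% | 6.3% | 230 |
| 0.10 | 1.22 | 169.9 | 77.5% | 7.6% | 253 |

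**Step 4: the district level.** This is a matter of structure, not arithmetic. Let each district have its own level and its own change over time. The difference in change between arms equals the intervention effect plus the difference between the two districts' own changes. The stable levels cancel because there is a baseline measurement. The district changes do not cancel, and one district per arm provides nothing from which to estimate their variance.

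**The case against.** **The model list is open and this is an article.** The models are given only as examples, and a full analysis plan may add a staff term. That stands as a possibility. But the text does more than stay silent: it commits to independent-sample tests and names the one correlation to be handled. The 85% holds only with no clustering, whatever model is used later.

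**The nesting and the SD are inferred.** The article does not say that each client has exactly one contact staff member, and it mentions high staff turnover in the sector. If 207 were a total, the implied SD would be 14.4. The 270 × 0.71 = 191.7 retained per arm would then give about 98% power, and still about 96% at a staff ICC of 0.10 with 3.18 clients each. The per-arm reading fits better. The objection limits how firmly the size can be stated; it does not change the direction.

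**Larger losses can be computed.** Dividing 270 by 65 gives 4.15 clients per staff member and, with n = 207, power of 74.3% and a type I error of 8.7% at an ICC of 0.10. That combines recruited clients per staff member with evaluable numbers per arm. The consistent cluster size is 3.18.

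**The limitation is partly disclosed.** The Discussion admits the lack of randomisation and the shortage of units, and Participants and setting says that the districts are alike in organisation and workforce. This stands. What is not said is that a change peculiar to one district is inseparable from the intervention effect and is absent from the p-values.

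**Conclusion.** The point holds with moderate size. For any positive staff-level correlation, the stated power and the unadjusted p-values are too favourable. For a staff ICC of 0.02 to 0.10, power is about 83.5% to 77.5% instead of 85%, and the type I error about 5.5% to 7.6% instead of 5%. At 0.01 the loss is 0.8 points. These figures rest on the assumed ICCs, the per-arm reading of 207, the back-solved SD and one contact staff member per client.

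Two stronger readings are not supported. A reader might infer that any difference between the districts is confounded with the intervention. The before/after design removes a stable difference when change is compared, so only district-specific change remains. A reader might also put a figure on the district problem: with 207 per arm, a district ICC of 0.005 or 0.01 gives a design effect of 2.03 or 3.06 and a type I error of about 17% or 26%. Those ICCs are pure assumptions that two districts cannot estimate, so the figures illustrate the mechanism and do not measure an error in the plan.

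**What to change.** 1. Record each older person's contact staff member at baseline and keep that link fixed for the analysis. Make a mixed model with a random intercept for staff, or GEE with staff as the cluster, the between-group analysis in place of the unadjusted independent-sample tests. If the contrast is group by time, let the staff effect vary by visit in the mixed model, because a constant intercept largely cancels from that contrast.
2. Restate the 85% as holding only without clustering, and give power over a small range of assumed ICCs, with the SD and the per-arm meaning of 207 written out.
3. State that the estimate is the difference in change between two particular districts, and limit causal conclusions to match. No model, and no further participants from the same districts, can remove this. A table over assumed district ICCs is optional and should be labelled illustrative.

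The cost is one identifier, one model term and revised wording, with somewhat wider confidence intervals and a lower stated power. No extra participants are needed if the lower power is accepted. Keeping 85% would take 217 to 253 evaluable per arm over ICCs of 0.02 to 0.10.
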